##### Microbial response to diet and supplementation

First, we will assess the microbiome response to each intervention within each group by comparing changes in microbiome composition between baseline (preintervention) and follow-up visits (visits 2–6). The gut profile will be compared between all four arms at each follow-up. The within-group changes from baseline will be compared between groups.

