## Methods

### Trial design and setting

This is a single-centered, partially randomized placebo-controlled double-blind feasibility trial with three intervention arms (Gutopia, Gutboost, and Gutless) and one active control. In total, 100 pregnant women with a history of depression and/or anxiety/PDA attending Sunnybrook Hospital Clinics in the Greater Toronto Area will be recruited.

Participants in Gutopia will receive a daily dose of both investigational products and dietary counseling on increasing dietary fiber. Participants in Gutboost will receive a daily dose of both investigational supplements, while participants in the Gutless arm will receive fish oil and a placebo. Participants in Gutless and Gutboost will be blinded to the status of the placebo/probiotic they will be receiving. The study member interacting with the patients will also be blinded to the treatment group the participant is assigned to. Participants who fully consent to receiving both investigational products, including placebo, will be fully randomized to one of the intervention arms. Participants not willing or able to take a placebo or probiotics will be assigned (not randomized) to the appropriate group that accommodates their preferences/needs. Participants unable or unwilling to take any of our investigational products will be assigned to the active control arm. Women in the control arm will receive standard care offered to all obstetric patients seen at the hospital.

The study involves six study visits, all of which can be conducted virtually every 3 months from the time of enrollment (**Figure 1**). The last study visit will happen between 9 and 12 months postpartum. Two of the study visits will occur during pregnancy [enrollment (visit 1) and third trimester (visit 2)], with the remaining occurring at 1, 3, 6, and 9 months postpartum. At all study visits, information on diet, mental health, physical activity, and sleep quality will be collected. Additionally, all participants will provide a stool sample at each visit, using our stool collection kits, which will be shipped to or dropped off at our center.

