### The intervention

Participants in all intervention groups will receive a 200-ml bottle of Genestra brand Super EFA Forte Liquid Omega-3 Fatty Acid. Participants will be instructed to take 1 teaspoon a day with a meal.

Participants in the Gutopia and Gutboost intervention groups will receive HMF Maternity Probiotic Formula, a Genestra brand. Participants will be asked to take one tablet daily with food.

Details of both supplements are provided under Investigational products in the following section.

Only participants in Gutopia will receive a dietary intervention. Intervention is geared toward increasing gut-friendly foods via a flexible dietary plan aimed at increasing daily uptake of prebiotic and probiotic foods. A registered dietitian will use baseline food questionnaire data provided by each subject at enrollment to devise strategies and recommendations for increasing intake of pre/probiotic foods. The target goal is to include at least 35 g/day of fiber and at least one to two servings of fermented foods daily. The dietary intervention will also include recommendations minimizing highly processed foods high in sugar and fat. To improve adherence and accountability, weekly follow-ups by phone, virtual meeting, or email will be conducted by a trained study team member until patients have reached a level of confidence in attaining goals. During each follow-up, the study team will monitor the level of adherence to the study RD’s recommendations. These follow-ups will be designed to provide encouragement while helping patients address and prevent triggers that jeopardize their fiber intake.

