#### Investigational products

All participants in treatment groups will receive a 200-ml bottle of Genestra brand Super EFA Forte Liquid Omega-3 Fatty Acid. This product contains a total of 2,600 mg of O3FA (1,500 mg of EPA + 1,000 mg of DHA) per 5-ml serving. The participant will be instructed to take 1 teaspoon a day with a meal. Each bottle contains about 40 servings, and a daily consumption of 1 teaspoon a day is expected to last 6 weeks. Each patient will receive supplies for the duration of the study period. While no clear upper tolerable dose in pregnancy has been identified, no increase in the risk of bleeding or complications at delivery has been observed in pregnant women (*n* = 533) receiving 2.7 g/day during the last trimester compared to women receiving olive oil or no supplements (26, 27). An updated review including 70 RCTs (19,927 participants) indicated a reduced risk of preterm birth for those tasking O3FAs compared to placebo or no intervention (28). The dose used in our trial is consistent with a dose that is likely effective and is below the safe maximum dose suggested in these trials.

We will use HMF Maternity Probiotic Formula, a Genestra brand. Each capsule contains 10 billion of four strains of bacteria: *Lactobacillus salivarius* (6.25 billion CFU), *Bifidobacterium animalis* subsp. *lactis* and *Bifidobacterium bifidum* (2.5 billion CFU), and *Lactobacillus paracasei* (1.25 billion CFU). While an updated review of evidence including seven trials (1,647 participants) indicates a possible increased risk of preeclampsia (29), a meta-analysis of several RCTs of probiotic use in pregnancy reported no increased risk to the fetus (30). Furthermore, the probiotic supplement in our trial was specifically labeled for pregnant women, following its use in a double-blind, placebo-controlled clinical trial of 454 pregnant women—no increase in adverse events in comparison to placebo was noted (31).

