The placebo capsules will contain 48% maltodextrin, 48% microcrystalline cellulose, 2% magnesium stearate, and 2% silicon dioxide. The capsule shell will be composed of hydroxypropyl ethylcellulose and will be identical in capsule shape and packaging to the probiotics. Participants will be instructed to take one capsule a day with food, 2–3 hours before or after taking an antibiotic in the event that one is prescribed through ancillary usual care received separate from study procedures. Each box of probiotics/placebo is expected to last 30 days. Participants will be provided with enough supplies for the duration of the study period.

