#### Statistical analysis

Should the trial succeed and we continue to recruit for a larger trial, the following statistical plan will be used to compare mental health outcomes between the groups: we will use mental health scores as the primary outcome and an intent-to-treat approach for these analyses.

Participants lost to follow-up will be assumed to have lost interest/commitment to the study and will be excluded from the analysis. Those who discontinue treatment will still be included.

Between-group differences for EPDS/GAD-7 scores will be analyzed using analysis of covariance (ANCOVA), with group membership as the independent variable, EPDS/GAD-7 as dependent, and pharmacotherapy, exercise status, and any form of psychotherapy as covariates.

The interaction effect between the O3FA and probiotics model will be analyzed and reported in each model. Alternative models will be used if the assumptions of ANCOVA are violated. If differences are found between groups, appropriate *post-hoc* analyses will be conducted to identify where the differences lie. Within-group differences at each time point will be analyzed using repeated measures ANOVA. Data from each follow-up will be compared to baseline scores. EPDS/GAD-7 scores will be the dependent variables, and follow-up times will be our independent variable.

Each stool sample will undergo shotgun metagenomics for taxonomic and functional output readings. A comprehensive analysis of all findings will be conducted by an experienced bioinformatics expert at Zymo Research. All researchers involved in the stool analysis will be blinded to the type of intervention. The relationship between each intervention and the relationship to EPDS and GAD-7 scores will be analyzed and reported by an experienced bioinformatician.

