## Discussion

Given the prevalence of PDA and its resulting impact on quality of life and infant well-being, the importance of investigating underutilized and overlooked nonpharmacological options is paramount. Specifically, the need to investigate alternative approaches in comparison to prescription medication and psychotherapy has been identified as an important need by expecting and new mothers. It is anticipated that pregnant women with a history of depression and anxiety will be particularly interested in partaking in this trial, resulting in favorable recruitment rates. Given the positive findings of O3FA and probiotic supplements on mental health symptoms in nonpregnant adults, we expect a similar trend in PDA symptoms, with a low likelihood of adverse events.

While not our main objective, we anticipate a correlation between the microbial composition and probiotics and O3FA supplementation. As several recent studies have demonstrated a positive impact of probiotics (19–21) or O3FAs (22, 23) on mental health outcomes via changes in the gut microbiome, this has yet to be demonstrated in individuals at risk of PDA. Having intervention groups that provide both supplements (Gutboost) versus O3FA alone (Gutless) will allow us to determine potential interaction between these supplements. We anticipate a difference in mental health scores between the Gutboost and Gutless intervention groups. Incorporating a third intervention arm where dietary counseling is provided in addition to supplementation (Gutopia) further allows us to understand the interaction between diet and supplementation. We anticipate differences in mental health scores between Gutopia compared to the other intervention arms. Additionally, having an active control arm can potentially inform the magnitude and directionality of these changes by comparing outcomes in the intervention arms (*N* = 75) to the active control arm (*N* = 25).

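### The exploratory microbiome response is whole-stool composition sampled during dosing, so taxon-level and presence/absence contrasts of the probiotic arms with Gutless or control can register the capsule's own four species

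*Protocol article*

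**What the plan says.** All places are in the protocol article.

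- **Who takes the bacteria.** The intervention: "Participants in the Gutopia and Gutboost intervention groups will receive HMF Maternity Probiotic Formula, a Genestra brand", one unit daily. Investigational products: "Each capsule contains 10 billion of four strains of bacteria", with *L. salivarius* the largest component.
- **Who does not.** Trial design and setting: "participants in the Gutless arm will receive fish oil and a placebo". The listed placebo ingredients include no bacteria: "The placebo capsules will contain 48% maltodextrin, 48% microcrystalline cellulose, 2% magnesium stearate, and 2% silicon dioxide". The control arm receives no study product.
- **When stool is taken.** Capsules are supplied throughout ("Participants will be provided with enough supplies for the duration of the study period"), and the Microbiome profiling section has stool collected at baseline and at every follow-up. No sample after a break from the product is described.
- **What is measured.** Statistical analysis: "Each stool sample will undergo shotgun metagenomics for taxonomic and functional output readings".
- **What counts as response.** Microbial response to diet and supplementation takes the change in composition between baseline and visits 2–6 within each arm, compares those changes between arms, and adds: "The gut profile will be compared between all four arms at each follow-up".
- **How it is to be read.** O3FA and probiotic interaction relies on the microbiome contrast of Gutboost with Gutless. The Discussion says "we anticipate a correlation between the microbial composition and probiotics and O3FA supplementation".
- **Status.** Outcomes measured calls the work exploratory, a search for signals to support a larger trial. Microbiome profiling calls the text a brief outline.

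**The concern.** The Background argues that benefit may come through restoring a healthy gut community, which is a statement about the host's own bacteria. The measured quantity is everything in the stool. In Gutboost and Gutopia that includes organisms swallowed shortly before sampling; in Gutless and control it does not. A difference in those species can therefore appear with no change at all in the resident community, and the correlation expected in the Discussion could be met, at least in part, by the capsule passing through.

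Two readings are at stake. A between-arm difference might be taken as an effect on the host community. An association of composition with EPDS or GAD-7 might be taken as support for a gut–brain mechanism when part of it could be an association with taking the capsule. Since these signals are meant to inform a larger trial, the two sources should be separable. Gutopia has a second source of ingested organisms, because its dietary plan aims at one to two servings of fermented foods a day.

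**Working it through.** **1. The plan's own figure.** Investigational products gives 6.25 billion CFU (*L. salivarius*), 2.5 billion (the two *Bifidobacterium* species together) and 1.25 billion (*L. paracasei*). 6.25 + 2.5 + 1.25 = 10.0 billion, which agrees with the stated total. The Discussion gives 75 women over three intervention arms and 25 controls; 75 / 3 = 25 per arm if the split is equal, which is an assumption.

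**2. Plausible read share (assumed inputs).** The documents give no stool load, DNA recovery or sequencing depth. Assume 10^12 to 3×10^13 stool bacteria per day, recovery of 1% to 100%, and 10 million reads.

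Share = daily dose × recovery / daily stool bacteria.

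- *L. salivarius*, low: 6.25×10^9 × 0.01 / (3×10^13) = 2.1×10^-6, or about 21 reads per 10 million.
- *L. salivarius*, high: 6.25×10^9 × 1 / 10^12 = 0.00625, or 62,500 reads per 10 million (about 0.6%).
- Whole capsule, high: 10^10 / 10^12 = 1%.

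Under these inputs the product is often detectable but makes up at most about 1% of reads.

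**3. Presence/absence of one capsule species.** Exact rejection rate of a two-sided Fisher test at 0.05, 25 versus 25, resident community identical. Detection rates are assumed.

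| Detected, probiotic arm vs Gutless | Rejects |
|---|---|
| 80% vs 10% | >99.9% |
| 50% vs 10% | 83% |
| 50% vs 20% | 51% |
| 10% vs 10% | 0.9% |

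**4. Presence/absence of the whole profile.** Jaccard PERMANOVA, 25 versus 25, no resident difference, four capsule species. At 80% versus 10% detection it rejects in about 100% of trials. With 200 resident species it rejects in 45–74% at 50% versus 10%, and in 24–38% at 50% versus 20%, depending on the assumed prevalence of the resident species. With equal detection it rejects in 3–8%.

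**5. Abundance-based tests.** Simulation of 25 versus 25 with 150 taxa and identical resident communities. The four capsule species together make up about 0.1% of the resident community, and product DNA is added to one arm at a median read share f (300 replicates). The taxon-level column is a Mann–Whitney test on the four species at 0.05/150. The whole-profile column is Bray–Curtis PERMANOVA at 0.05 with 199 permutations.

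| f | At least one capsule species significant | Bray–Curtis, full profile | Bray–Curtis, four species removed |
|---|---|---|---|
| 0 | 0% | 5% | 6% |
| 0.01% | 9% | 6% | 7% |
| 0.1% | 99.7% | 6% | 7% |
| 1% | 100% | 12% | 5% |
| 5% | 100% | 99% | 3% |

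After the four species are removed and the rest renormalised, at least one remaining taxon is significant (Bonferroni) in 2–4% of trials at every f. The filter therefore restores near-nominal error in this setting.

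**6. Which contrasts are exposed.** Gutboost or Gutopia against Gutless or control, where one side takes the capsule. Gutopia against Gutboost and Gutless against control do not differ in the capsule.

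**The case against.** The strongest reply is that this is silence and not error. The article fixes no metric, taxonomic level or filter, calls its text a brief outline, and leaves the analysis to a bioinformatician; an unseen analysis plan may remove the administered species. A reader might infer that the sponsor has decided to count the product as response. The article does not say so. What remains is that the response is expressed as overall composition, and that the interaction section and the Discussion draw on the very contrast in which one arm swallows the measured organisms. Whether response includes the product decides what the comparison means, so it is more than a pipeline detail.

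A reader might also infer that a positive result would mainly show adherence or could discriminate nothing. That does not follow. Rates near 100% belong to particular detection pairs or read shares, none of them in the documents. At shares up to the 1% implied by the inputs in step 2, the abundance-weighted whole-profile test rejects in only 5–12% of trials; at 0.01% even the taxon-level test rejects in 9%. Changes in other taxa would remain informative.

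It can further be argued that persistence of supplied species is part of the response; the Background itself cites a rise in *Lactobacillus* as a sign of restoration under omega-3 in rodents. This stands as a reason to keep the full profile beside the filtered one. Finally, nothing is lost by waiting, since shotgun data keep every taxon and can be filtered later. That is true, but stating the rule before results are known is what protects the interpretation.

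**Conclusion.** The point holds in a limited form. As written, taxon-level and presence/absence contrasts of Gutboost or Gutopia with Gutless or control can reflect recovery of the four capsule species without any change in the resident community. Abundance-weighted whole-profile distances are little affected unless the product reaches a few percent of reads. The result would be ambiguous between product recovery and host change.

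The qualitative conclusion needs only the stated design: dosing during sampling, whole-stool sequencing, and composition as the response. The size rests on assumed read shares, detection rates, arm sizes of 25 and simulated communities.

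Severity is minor. The primary outcome is process evaluation, the microbiome aim is exploratory, and the between-arm comparisons of EPDS and GAD-7 scores do not use the microbiome data.

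**What to change.** In Microbial response to diet and supplementation, state that the within-arm and between-arm composition comparisons, and the associations with EPDS and GAD-7, are run twice: on the full profile, and after removing reads assigned to *L. salivarius*, *B. animalis* subsp. *lactis*, *B. bifidum* and *L. paracasei* in all arms and at all visits, with renormalisation. Base any statement about change in the host community or a gut–brain mechanism, including those in O3FA and probiotic interaction and in the Discussion, on the filtered result. Report the four species separately as an exposure marker, which also supports the planned monitoring of compliance.

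The cost is one filtering step and a few sentences, with no new samples. Samples can be shipped as one batch at study end, so the rule can be set before any sequencing result exists. The downside is that the filter also removes resident members of the same species, which is why both versions are shown. It does not remove fermented-food organisms of other species in Gutopia, so it is cleanest for Gutboost versus Gutless, and the Gutopia contrasts should carry that caveat.

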##### Microbiome and mental health

We will measure the interaction between diet and supplementation. The objective is to understand the differences in microbial and metabolic profiles of each group in response to the interventions and the corresponding changes in mental health scores.

##### O3FA and probiotic interaction

The synergism between O3FAs and probiotics has not been defined. We expect that comparing the microbiome between Gutboost and Gutless will yield differences between O3FA alone and O3FA + probiotics on mental health scores.

#### Statistical analysis

Should the trial succeed and we continue to recruit for a larger trial, the following statistical plan will be used to compare mental health outcomes between the groups: we will use mental health scores as the primary outcome and an intent-to-treat approach for these analyses.

Participants lost to follow-up will be assumed to have lost interest/commitment to the study and will be excluded from the analysis. Those who discontinue treatment will still be included.

Between-group differences for EPDS/GAD-7 scores will be analyzed using analysis of covariance (ANCOVA), with group membership as the independent variable, EPDS/GAD-7 as dependent, and pharmacotherapy, exercise status, and any form of psychotherapy as covariates.

The interaction effect between the O3FA and probiotics model will be analyzed and reported in each model. Alternative models will be used if the assumptions of ANCOVA are violated. If differences are found between groups, appropriate *post-hoc* analyses will be conducted to identify where the differences lie. Within-group differences at each time point will be analyzed using repeated measures ANOVA. Data from each follow-up will be compared to baseline scores. EPDS/GAD-7 scores will be the dependent variables, and follow-up times will be our independent variable.

Each stool sample will undergo shotgun metagenomics for taxonomic and functional output readings. A comprehensive analysis of all findings will be conducted by an experienced bioinformatics expert at Zymo Research. All researchers involved in the stool analysis will be blinded to the type of intervention. The relationship between each intervention and the relationship to EPDS and GAD-7 scores will be analyzed and reported by an experienced bioinformatician.

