#### Criteria for study withdrawal

All eligible participants will be informed that their participation is completely voluntary, and they can discontinue participation at any time. Participants may withdraw from the study entirely or from specific parts of the study only. If the latter is desired, then follow-up pertaining to other consented components of the study will continue.

Data collected prior to withdrawal may be retained and used in a manner consistent with the study purpose and protocol. The exception is if participants explicitly request the removal of all previously collected information and data, in which case the study team will oblige. Once a participant expresses a desire to withdraw from the study, the research team member in contact with the participant will confirm whether previously collected data can be retained (or should be destroyed) and whether the participant can be contacted in the future for other research opportunities.

The participant will be notified during consent and at the time of withdrawal that any data retained for the analysis cannot be withdrawn after study closure or publication of the study (whichever comes first). Lost to follow-up is defined as enrolled participants that were randomized and completed all parts of visit 1, but completed zero parts of any subsequent visits (2, 4–7). Five attempts will be made to reschedule the study visits for these participants. The number of attempts and modes of communication to reach these participants will be documented. If the missed study visit is not successfully rescheduled within 4 weeks, the visits will be marked as lost to follow-up. Should the participant return to completing the later visits, they will be included in all analyses consistent with the intention to treat. However, if all attempts to reconnect by the study team fail for the missed visit and all remaining visits, and/or if the participant explain that they wish to stop participating in the study, they will be marked as study withdrawal.

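### The planned analysis is called intent-to-treat yet excludes women lost to follow-up, and the definition of that group lists the wrong visits and covers only randomised women

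*Protocol article*

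**What the plan says.** The Statistical analysis section applies if the feasibility trial succeeds and recruitment continues. For that case it says "we will use mental health scores as the primary outcome and an intent-to-treat approach for these analyses". Its next paragraph says "Participants lost to follow-up will be assumed to have lost interest/commitment to the study and will be excluded from the analysis", followed by "Those who discontinue treatment will still be included".

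The group to be excluded is defined under Criteria for study withdrawal. That text begins "Lost to follow-up is defined as enrolled participants that were randomized and completed all parts of visit 1" and adds the condition that they "completed zero parts of any subsequent visits (2, 4–7"). The same section then does three further things:

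- It marks a single missed visit, if not rescheduled within 4 weeks, as lost to follow-up.
- It promises that a woman who returns for later visits is kept in every analysis, in line with intention to treat.
- It classes a woman who cannot be reached for the missed visit and all remaining visits as a withdrawal.

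On the schedule, Trial design and setting says "The study involves six study visits". Randomization and baseline evaluation makes visit 1 the baseline and places visit 3 at about 4 to 6 weeks postpartum. The section on microbial response gives the follow-up visits as 2 to 6.

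On methods, between-group differences in EPDS and GAD-7 are to be analysed by ANCOVA. For change over time the plan says "Within-group differences at each time point will be analyzed using repeated measures ANOVA".

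**The concern.** An analysis that removes randomised women because they stopped attending is not intent-to-treat, so two statements in the same section cannot both be followed. The reason given for loss is a presumption. The protocol itself foresees side effects and significant worsening of anxiety or depression (Criteria for study withdrawal), and its Background cites relapse rates of 40%. It does not say how often these would lead to loss. But where the outcome is a mood score, loss cannot simply be declared unrelated to it.

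The definition that triggers the exclusion is also faulty. Its visit list does not match the schedule, it is limited to randomised women in a trial where many are assigned, and the same term has more than one meaning within one section. Two analysts following the text could arrive at different analysis sets. Since the protocol foresees continuing enrolment into the larger trial, the rule should be settled before outcome data accumulate.

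**Working it through.** The protocol gives no loss rate, power or effect size, so there is no stated figure to reproduce. The check sets the texts side by side, with one illustrative calculation.

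**1. Visit list.** Follow-up visits by the schedule: {2, 3, 4, 5, 6}. Visits in the definition: {2, 4, 5, 6, 7}. Visit 3 is left out, and visit 7 does not exist.

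**2. What the rule does to particular women.** All rows assume that visit 1 was completed.

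| Woman | Meets the definition as written? | Consequence |
|---|---|---|
| Randomised, attends only visit 3 | Yes | Excluded, although she has a postpartum score; conflicts with the promise to keep women who return |
| Randomised, attends nothing after visit 1 | Yes | Excluded; conflicts with the intent-to-treat label |
| Assigned control, attends nothing after visit 1 | No (not randomised) | Rule does not apply |
| Assigned by preference to an intervention arm, attends nothing after visit 1 | No (not randomised) | Rule does not apply |

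The last two rows follow from Trial design and setting. Women who will not or cannot take placebo or probiotics are assigned without randomisation, and women who will not or cannot take any study product are assigned to control. The Discussion puts 25 women in the control arm and 75 in the intervention arms.

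**3. Overlapping terms.** A randomised woman with nothing after visit 1 who cannot be reached fits both the lost-to-follow-up definition and the withdrawal category. The Statistical analysis section excludes the first and does not mention the second. A woman with one missed visit that is not rescheduled carries the lost-to-follow-up mark for that visit. The exclusion sentence does not say which use of the term it means.

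**4. Repeated-measures ANOVA (illustration).** Suppose each of the five follow-up visits is missed independently with probability m. Both m and independence are assumptions. The share of women with all five scores is (1 − m)^5:

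- m = 5%: 0.95^5 = 0.774, or 77% complete
- m = 10%: 0.90^5 = 0.590, or 59% complete
- m = 15%: 0.85^5 = 0.444, or 44% complete

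In its classical form, without imputation, the method uses only women with complete data. The remaining 23%, 41% or 56% would be left out of the within-group analysis, although the protocol promises that those who miss a visit and return are kept in every analysis.

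**The case against.** The strongest reply has four parts.

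*The plan is conditional.* It is for a larger trial, and the present study's primary outcome is process evaluation. This stands, and it limits what is at stake now. But the faulty definition sits in a section that governs the current study.

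*Excluded women have nothing to analyse.* With the list corrected to visits 2 to 6, a lost woman has no post-baseline score and would drop out of an available-case ANCOVA with or without the rule. This also stands. A reader might infer that the exclusion itself biases the arm comparison. For example, 10 to 20 percentage points of differential loss, with lost women scoring 2 to 4 EPDS points differently, gives 0.10 × 2 = 0.2 to 0.20 × 4 = 0.8 points. The documents do not support that reading. Every input is assumed, the result is ordinary attrition bias, and deleting the sentence would not remove it.

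*Retention is measured elsewhere.* A reader might infer that the loose definition overstates retention. Nothing in the protocol defines retention as the complement of lost to follow-up. Outcomes measured already lists the proportion of study visits completed, as well as numbers screened, randomised and enrolled.

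*Some of this is loose drafting or belongs in a SAP.* The word *randomised* may be shorthand, since Randomization and baseline evaluation uses it just after speaking of women randomised or assigned. The promise to keep returning women suggests that the visit-3 case was not intended. Missing-data handling may also be set out in a SAP. But the exclusion rule and its definition are fixed in the protocol and conflict with other text there, so a SAP could not follow both.

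**Conclusion.** The point holds on the text. The intent-to-treat label and the exclusion contradict each other, the reason for loss is assumed, and the visit list is wrong at two places (visit 3 omitted, visit 7 non-existent). The definition cannot apply to women who were not randomised, and the term overlaps with its visit-level use and with withdrawal.

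The practical harm is an analysis set that is mislabelled and ambiguous, unequal rules for randomised and assigned women, and an untested assumption about missing outcomes. No bias of a stated size can be attributed to the exclusion, and no overstatement of retention follows from the text.

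The repeated-measures ANOVA part is an inference about the classical method, because the protocol does not say that women with a missed visit are dropped. It concerns within-group change only, so the 77%, 59% and 44% say nothing about the between-arm ANCOVA, and they rest on assumed, independent miss rates. Nor would it be accurate to say that the exclusion acts on the intervention arms as a whole, since some women in those arms are assigned and also escape it.

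**What to change.** 1. Delete the exclusion sentence and the assumed reason for loss.
2. Define lost to follow-up as no part of visits 2 to 6, for all enrolled women in all four arms. Use a different term for a single missed visit, and state how the definition relates to withdrawal and how withdrawn women are analysed.
3. Analyse all allocated women with at least one score by a likelihood-based mixed model for repeated measures that uses every available visit. Keep comparisons among randomised women separate from comparisons that involve assigned women. A model restricted to randomised women would leave out the assigned controls and the women placed by preference.
4. Add one missing-not-at-random sensitivity analysis for women with no follow-up score, because the main model learns almost nothing about their outcomes. Otherwise, call the analysis set modified intent-to-treat and say who is left out.

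The cost is revised wording and a little more analysis in standard software. No new data are needed.
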